### Postoperative

- POD at arrival in intensive care unit (ICU), POD 1 and 4Blood chemistry samplesCalculation of eGFR (according to MDRD)ABG at arrival in ICU, at 3–6–12–24 h after surgery. Data collection on serum lactates, pH, paO_2_, paCO_2_, BE, HCO_3_−, calculation of the Pa/Fi ratioChest X-ray and evaluation of eventual pulmonary damage through Murray “Lung Injury Score” (LIS) [23]. The score considers 4 criteria for the development of ALI/ARDS: hypoxemia, respiratory system compliance, chest radiographic findings and the positive expiratory pressure level. Each criteria receives a score from 0 to 4 according to the gravity of the condition. The final score is obtained dividing the collective score by the number of components used. A score equal to 0 shows the absence of pulmonary damage, a score between 1 and 2.5 shows a mild to moderate pulmonary damage and a final score major than 2.5 shows the presence of ARDS.Monitoring of estubation time (hours)Calculation of VISmaxMonitoring of postoperative cardiac function at POD 4 through echocardiogram and evaluation of LVEFMonitoring of postoperative stroke; a diagnosed stroke by a neurologist according to clinical, radiological (CT scan and/or MRI) and electrophysiological examination (EEG). Patients affected by stroke will undergo “modified Rankin Scale” (mRS) calculation which evaluates the degree of disability following a stroke and will be compared to the preoperative mRS. The score goes from a minimum score of 0 (no disability) to 6 (death).Evaluation of acute kidney injury according to the definition of “Acute Kidney Injury” (AKIN) [27] through a stratification of renal damage in three stages: [1] Creatinine × 1.5–2.0 from baseline or Creatinine increased by at least 0.3 mg/dl (26.5μmol/L) [2]; Creatinine × 2.0–2.9 from baseline [3]; Creatinine > 3.0 from baseline or Creatinine increased at least 4 mg/dl (353.6 μmol/l) or the initiation of dialysis.Monitoring of gastrointestinal ischaemia: a diagnosed ischaemia by a surgery consultant according to the value of serum lactate, WBC, clinical and radiological (CT scan and/or abdomen ultrasound) examination.Monitoring of in-hospital death

- Follow-up visit at 30 days from surgery:Stroke and eventual transitory or permanent neurological damage (mRS score)Acute kidney injury (eGFR and AKIN score)Cardiac function (LVEF)Re-hospitalizationDeath for cardiovascular or other causes.

All the procedures listed above are considered the standard of care in the clinical practice at the Cardiac Surgery Divisions of all the Participating Centres.

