#### Secondary objectives

To assess the intraoperative outcomes, through the following perfusion parameters:Intraoperative cerebral perfusion (through monitoring of the NIRS values)Intraoperative pulmonary perfusion (through Pa/FiO_2_ ratio, paO_2_, paCO_2_ at blood gas analysis, and VO_2_R and DO_2_ at CDI® Blood Parameter Monitoring System 550)

To assess postoperative clinical outcomes, through the following parameters:Intraoperative and postoperative low cardiac output syndrome (according to the values of vasoactive inotropic score, VIS) [22]Postoperative cardiac function (measuring left ventricular ejection fraction, LVEF)Postoperative respiratory failure (through the values of Lung Injury Score, LIS, scale) [23]Postoperative stroke and entity of transitory or permanent neurological damage (through score of modified Rankin Scale—mRS) [24]Postoperative acute kidney injury (through AKI score)Postoperative hepatic failure (measuring the hepatic function and coagulation indices)Postoperative gastrointestinal ischaemiaPostoperative cardiovascular death, or death due to other causes

To assess clinical outcomes at 30 days from surgery:Stroke and entity of the transitory or permanent neurologic damage (mRS score)Acute kidney injury (AKI score)Cardiac function (LVEF)Re-hospitalizationDeath for cardiovascular or other causes

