### Statistical methods

#### Statistical methods for primary and secondary outcomes {20a}

Demographic and clinical characteristics will be presented as percentage in case of ordinal variables and as percentages, means, medians and standard deviations and/or interquartile range in case of categorical and/or quantitative variables. The Pearson *χ*^2^ and the *H*-test by Kruskal-Wallis will be used for any assessment of differences between the three groups. To evaluate the primary endpoint of the study, the Mann-Whitney test will be used for comparisons between groups with an alpha equal to 0.01667. The Mann-Whitney test will also be used to evaluate the secondary endpoint obtained by AUC, while the Pearson *χ*^2^ will be used to compare the proportion of cases above and below the serum lactate peak cut-off > 3mmol. To compare the secondary endpoints in the three groups according to the types of variables, ANOVA or non-parametric *H*-test by Kruskal-Wallis will be used for quantitative variables, while the Pearson *χ*^2^ test will be performed for dichotomous or categorical variables. ANOVA for repeated measures, or Friedman test or the mixed effects model will be used for variables collected at different timepoints. A *p*-value < 0.05 will be considered statistically significant. Both an intention to treat (ITT) and per protocol (PP) analysis will be performed.

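### The stated before-and-after mRS comparison cannot be made for a first stroke, and a between-arm mRS test in stroke patients alone would not be a randomised comparison

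*Protocol article*

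**What the plan says.** Four parts of the protocol article decide who has an mRS, and they do not agree.

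- **Secondary objectives.** The aim is "Postoperative stroke and entity of transitory or permanent neurological damage (through score of modified Rankin Scale—mRS"), which covers transient as well as lasting damage.
- **Preoperative procedures, day before surgery.** A preoperative mRS is taken only if the patient has had a stroke before.
- **Postoperative procedures.** "Patients affected by stroke will undergo “modified Rankin Scale” (mRS) calculation which evaluates the degree of disability following a stroke", and the result "will be compared to the preoperative mRS". The same section states: "The score goes from a minimum score of 0 (no disability) to 6 (death"). The 30-day visit lists "Stroke and eventual transitory or permanent neurological damage (mRS score") and does not say that every patient is scored.
- **Secondary outcomes.** Neurological dysfunction is a dichotomous outcome. The mRS is added only for permanent injury, which is narrower than both the objectives and the procedures.

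The statistical methods section contains a general sentence, "To compare the secondary endpoints in the three groups according to the types of variables", followed by tests chosen by variable type. It promises both an intention-to-treat and a per-protocol analysis. It does not single out mRS for different handling.

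**The concern.** There are two separate problems.

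**Baseline.** The procedures promise a comparison with a preoperative score that sites are told not to collect unless there is a stroke history. An analysis plan cannot supply a measurement that was never taken.

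**Who is compared.** Randomisation takes place the day before surgery, so a postoperative stroke is a post-randomisation event. The assigned pressure may affect it: the Background itself cites a trial with more strokes at 70–80 mmHg. If the general rule for secondary endpoints is applied to mRS, the arms are compared only in patients who had a stroke. An arm that adds mild strokes lowers its own mean score, and an arm with few but severe strokes looks worse. Nor does the text give a score to patients without a stroke, or to those who die without one, although the scale counts death as 6.

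At stake is the reading of the mRS, the only measure of the extent of neurological damage named in the secondary objectives.

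**Working it through.** The document gives no planned figure for mRS, so there is none to reproduce. The check sets the sections side by side and then sizes the effect.

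**Step 1. Baseline.**

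| Patient | Preoperative mRS | mRS after postoperative stroke | Stated comparison possible? |
|---|---|---|---|
| Past stroke, new stroke | yes | yes | yes |
| No past stroke, new stroke | no | yes | no |
| No postoperative stroke | only if past stroke | none prescribed | not applicable |

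The second row cannot be completed as written, and the text does not say that a missing baseline counts as 0.

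**Step 2. How many patients would be scored.** Inputs: 333 per arm (Sample size) and stroke rates of 1.1% and 7.0% (Background, from one cited trial, P=0.09; used only as a range).

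- 333 × 0.011 = 3.7, about 4 patients
- 333 × 0.070 = 23.3, about 23 patients

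With the 300 per arm before the drop-out allowance, the numbers are 300 × 0.011 = 3.3 and 300 × 0.070 = 21.

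**Step 3. How many of those have a baseline.** Number with a baseline = 300 × stroke rate × share with a past stroke. The share is not given; 5% to 30% is assumed.

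- At 1.1%: 3.3 × 0.05 = 0.2 to 3.3 × 0.30 = 1.0 per arm
- At 7.0%: 21 × 0.05 = 1.1 to 21 × 0.30 = 6.3 per arm

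Under that assumption, 70% to 95% of scored patients lack a baseline. They are the majority for any share below 50%.

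**Step 4. Can the direction reverse?** The scores are assumed. Arm A has 4 strokes scored 3, 4, 4, 5. Arm B has the same four plus 19 mild strokes, ten scored 1 and nine scored 2.

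| Analysis | Arm A | Arm B | p |
|---|---|---|---|
| Mean mRS, stroke patients only | 16/4 = 4.00 | (16 + 10 + 18)/23 = 44/23 = 1.91 | 0.007 (Mann-Whitney) |
| Mean over all 333, no stroke = 0 | 16/333 = 0.048 | 44/333 = 0.132 | 0.0002 (Mann-Whitney) |
| Stroke yes/no, all 333 | 4/333 | 23/333 | 0.0002 (Pearson χ²) |

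The stroke-only analysis favours arm B, which has 19 more strokes. Both all-randomised analyses favour arm A.

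**Step 5. Low stroke rates.** With 3 scored patients in each of two arms, the smallest two-sided exact Mann-Whitney p is 2/C(6,3) = 2/20 = 0.10. A significant but misleading result then cannot arise in such a pair, and the comparison also tells the reader very little.

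**The case against.** The best counter-argument is that the protocol already contains the outcome that guards against a wrong conclusion. Neurological dysfunction is listed as a dichotomous secondary outcome, dichotomous outcomes go to a χ² test, and an intention-to-treat analysis is promised. In the illustration above that test gives p = 0.0002 against the arm with more strokes. This stands, and it limits the point to severity. A reader might infer that an arm causing extra strokes would simply come out looking better in this trial. The documents do not support that, because stroke incidence can be compared separately in everyone randomised.

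The illustration is also built to show a reversal: every extra stroke is mild, the scores are invented, and the rates come from one study whose difference had P=0.09. If only permanent injury is scored, some mild cases might drop out. This stands too. The example shows that the two analyses can disagree in direction, not that they will.

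It can further be said that no mRS test is named and that handling a conditional score is work for an analysis plan. This is partly right. But the general sentence covers secondary endpoints without exempting mRS, and the missing baseline is a matter of data collection.

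Finally, a preoperative score only after an earlier stroke may be meant to separate old stroke disability from new. That is a sensible purpose, but it does not supply the comparison promised for a first stroke. A reader might also take it as established that most scored patients lack a baseline, or that limitation from heart disease will be read as stroke damage. The first is an inference, since the share with a past stroke is not given, and the second is possible but not shown.

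**Conclusion.** The point holds in a limited form and is minor. Two things follow from the text alone: the stated comparison with a preoperative mRS cannot be made for a first stroke, and the sections disagree on whether stroke, any neurological damage or only permanent injury triggers scoring. A third follows if the general rule for secondary endpoints is applied to mRS: the between-arm comparison would be conditional on a post-randomisation event, would not be a randomised comparison, would not fit the stated intention-to-treat analysis, and could point the opposite way from the all-randomised result.

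On the cited rates it would rest on about 4 to 23 patients per arm of 333. The size of any distortion depends on assumed scores and borrowed rates and cannot be fixed from the document. The primary endpoint, the sample size and the yes/no neurological outcome are unaffected.

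**What to change.** 1. **Analysis.** In the secondary outcomes and statistical methods, make any between-arm disability comparison in all randomised patients. One example is stroke with an mRS worse than before surgery, or death, by day 30, with patients who have neither counted as no event. State that mRS among stroke patients is reported descriptively only.
2. **Data collection.** Record the preoperative mRS in every newly enrolled patient at the existing preoperative assessment.
3. **Wording.** Reconcile the secondary objectives, the preoperative and postoperative procedures and the secondary outcomes on who is scored.

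The cost is a minor amendment and a minute or two per patient. Recruitment began in 2021, so patients already treated who had no past stroke will have no measured baseline. They stay in the all-randomised denominator, and the plan should state in advance how a stroke in one of them is counted.

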### Criteria for discontinuing or modifying allocated interventions {11b}

If any of the following clinical situations occur during the study period in patients already enrolled, this will be reason for exclusion of the patient from the study: withdrawal of consent by the patient, unplanned additional procedures, necessary during surgery for complications in itinere (not provided in the preoperative planning), the need of mechanical circulatory support > 72 h.

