#### Methods in analysis to handle protocol non-adherence and any statistical methods to handle missing data {20c}

Missing data will be handled by different data imputation methods (IPW-inverse probability weighting and LCOF-Last-Observation-Carried-Forward method) with sensitivity analysis.

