## Discussion

This randomized controlled trial is designed to investigate the MAP management during CPB in cardiac surgery, since it remains one of the “grey zone” of cardiac surgery. Providing and adequate tissue perfusion is the main goal of CPB during cardioplegic arrest. Nonetheless, some patients still reported ischaemic complication after heart operations. To date, only single-centre studies have been reported with small sample sizes, selected populations and contradictory findings. We started recruiting the first patients in 2021; however, during the first years of the study, we encountered some practical problems. Due to supply issues, we were without access to the CDI monitoring for a long period, causing us to slow down patient recruitment based on the availability of monitoring equipment. Additionally, it was not always easy to maintain the pressure within the range established by the randomization group, due to specific alterations in the arterial resistance of the patients (e.g. deep vasoplegia in “high MAP” or hypertension in “standard MAP”). So far, two patients have dropped out of the study for this reason. However, this trial is the first prospective multicentre randomized controlled study that compare three strategies of MAP management during CPB using the serum lactate peak as primary endpoint. Finding the most adequate approach will contribute to improve the outcome of patients undergoing heart surgery.

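### The exclusion rule in {11b} removes randomised patients from the study for post-randomisation complications, which conflicts with the promised intention-to-treat analysis and leaves the comparison open to arm-dependent bias

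*Protocol article*

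**What the plan says.** All references are to the protocol article.

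- **Procedures, Preoperative:** consent and randomisation both take place on the day before surgery.
- **Criteria for discontinuing or modifying allocated interventions {11b}:** where a listed event arises after enrolment, the text states that "this will be reason for exclusion of the patient from the study: withdrawal of consent by the patient, unplanned additional procedures". The procedures meant are those that an intra-operative complication makes necessary and that were not planned beforehand. The remaining trigger is "the need of mechanical circulatory support > 72 h".
- **Statistical methods {20a}:** "Both an intention to treat (ITT) and per protocol (PP) analysis will be performed". The article defines neither set.
- **Handling of non-adherence and missing data {20c}:** "Missing data will be handled by different data imputation methods", namely inverse probability weighting and last observation carried forward. Patients excluded under {11b} are not mentioned.
- **Discussion:** pressure could not always be kept in the assigned range, with arm-specific examples ("e.g. deep vasoplegia in “high MAP” or hypertension in “standard MAP"), and the article then reports: "So far, two patients have dropped out of the study for this reason".
- **Outcomes {12}:** the primary endpoint is peak lactate (Lmax) during cardiopulmonary bypass. Secondary outcomes include low cardiac output syndrome, kidney injury, gastrointestinal ischaemia and death.

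**The concern.** Section {11b} is headed as a rule on stopping or modifying the intervention, but its text takes the patient out of the study. It does not limit the removal to the per-protocol set. Withdrawal of consent is not at issue. The other two triggers are clinical events that follow randomisation and may follow from the assigned pressure. Prolonged mechanical support is close to the low-output outcome, and plausibly to kidney injury, gut ischaemia and death.

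If the rule is applied as written, the analysed patients are selected partly by how they fared. Should the arms differ in how often the triggers occur, an arm that loses more high-lactate or complicated patients will look better than it is. The 10% drop-out allowance in {14} protects the number of patients, not the comparability of the arms.

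The two drop-outs in the Discussion suggest that practice may be wider than the rule, since failure to hold MAP is not on the {11b} list.

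**Working it through.** **1. The plan's own sample size.** Inputs from {14}: SD 0.7, difference 0.19, alpha 0.05/3 = 0.01667 (two-sided), power 80%.

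n per group = 2 × [0.7 × (2.394 + 0.842) / 0.19]² ≈ 284.2. Dividing by the Mann-Whitney efficiency 3/π = 0.955 gives 297.6, so 298. With the unrounded difference 0.15 × 1.25 = 0.1875 the result is 306. The stated 300 is reproduced. 300 / 0.9 = 333.3, against the stated 333. The point therefore does not rest on a sample-size error, and keeping all randomised patients does not change these figures.

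**2. Passages side by side.** Randomisation comes first (day before surgery). The triggers come during surgery, or more than 72 h into mechanical support. The consequence is exclusion from the study. The promised analysis is ITT. A set that lacks randomised patients because of events after randomisation is not an ITT set. Lmax is measured during bypass, so it will already exist when support passes 72 h, and often when an unplanned procedure is needed. Exclusion then discards an observed primary value.

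**3. Illustration of size, no true effect.** From {14}: mean 1.25, SD 0.7. Assumed: log-normal shape, exclusion probability proportional to Lmax^1.5, and the exclusion rates.

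- Log-scale variance: s² = ln(1 + (0.7/1.25)²) = ln(1.3136) = 0.2728.
- Mean Lmax of excluded patients: 1.25 × exp(1.5 × 0.2728) = 1.88 mmol/l.
- Mean of retained patients at exclusion rate e: (1.25 − e × 1.88) / (1 − e).

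| Excluded, arm A vs B | Retained means | Spurious difference (B − A) | Share of 0.19 |
|---|---|---|---|
| 2% vs 8% | 1.237 vs 1.195 | −0.042 | 22% |
| 3% vs 6% | 1.230 vs 1.210 | −0.021 | 11% |

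**4. Effect on the planned test.** The primary test is Mann-Whitney, so a second simulation under no effect used that test at 0.01667, with 333 per arm and 1,500 runs per scenario. The highest-risk fraction of each arm was excluded. The assumed correlation between exclusion risk and log Lmax ran from 0.3 to 1.0, where 1.0 is the extreme case of lactate alone deciding exclusion. The Monte Carlo standard error at the nominal level is √(0.0167 × 0.9833 / 1500) ≈ 0.003.

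| Excluded | Bias in mean (mmol/l) | Type I error |
|---|---|---|
| 5% vs 5% | about 0 | 0.013 to 0.021 |
| 2% vs 5% | −0.014 to −0.053 | 0.015 to 0.052 |
| 5% vs 10% | −0.018 to −0.067 | 0.026 to 0.109 |
| 2% vs 10% | −0.029 to −0.117 | 0.031 to 0.252 |

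**5. Clinical outcomes, mechanism only.** The article gives no event rates. Suppose a true rate of 4% in both arms, and that half of the excluded patients have the event. Excluding 1% leaves (4 − 0.5)/99 = 3.5%. Excluding 4% leaves (4 − 2)/96 = 2.1%. The arm with more exclusions looks safer although nothing differs.

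**The case against.** - **A reader might infer that the ITT analysis is lost or impossible.** The article does not support that. It commits to both analyses and does not say that data already collected are discarded. Lmax will often exist, and data come from hospital records ({18a}, {19}). What stands is that the two sections are unreconciled. An analysis plan not shown may define the sets, but such a definition would still meet a rule that takes the patient out of the study, and it cannot supply 30-day assessments that were never made.
- **A reader might infer that the comparison is already biased, in a known direction.** No exclusion rates by arm are given. The Discussion's examples concern both the high and the standard arm, so even the sign is unknown. With equal exclusion the simulated bias is about zero.
- **A reader might take the two drop-outs as removals under a rule.** The Discussion is a progress note. It does not say who decided, in which arm, or whether data were kept. It supports the concern but does not establish a second rule.
- **The illustrated effect on Lmax may be modest.** The population is elective and of limited risk (EuroSCORE II below 9%, LVEF at least 40%), so large differences in exclusion may not arise, and at 2% vs 5% with weak correlation the test stays near nominal. The trial also calls itself exploratory. These points limit the size, not the contradiction.

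**Conclusion.** Section {11b} is wrong as written. It excludes randomised patients from the study for events that the assigned MAP could influence, and this conflicts with the ITT analysis in {20a}. This is a stated rule, not detail left to another document. The consequence is exposure to arm-dependent bias, not a demonstrated bias.

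The figures of about −0.04 and −0.02 mmol/l (22% and 11% of the planned difference), the type I error ranges and the clinical-outcome example all rest on assumed exclusion rates and on an assumed link between exclusion and outcome. The case for change rests on keeping randomised patients in the comparison, not on any one of these numbers.

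**What to change.** Amend {11b} and bring {20a} into line:

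- Record unplanned procedures, mechanical support beyond 72 h and MAP outside the assigned range as protocol deviations that do not remove the patient from the study.
- Follow every randomised patient to day 30 and analyse each in the assigned arm in the ITT analysis.
- Use these deviations only to define the per-protocol set, and report them by arm.
- Let only withdrawal of consent stop further data collection, keeping data up to that point where consent allows.
- Retrieve the data of the two patients reported as dropped out, where consent allows, and state their arms.

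The cost is an amendment and data retrieval for a few patients. Procedures are described as standard care and data come from electronic records, so nothing is added for patients and the sample size is unchanged. Recruitment is expected to run to 31/12/2026, so an early amendment limits further loss. No change to the clinical management of MAP is proposed.
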